## Abstract

Miracle Berry (MB) contains miraculin, a glycoprotein that alters sour tastes into sweet. MB may enhance the taste perceptions of hypo‐palatable foods (e.g., sour/bitter fruits and vegetables) and hyper‐palatable foods (e.g., sugar‐sweetened beverages (SSBs)), potentially influencing their liking and intake. Therefore, this study aims to assess the effects of different doses of MB on the taste perception, overall liking and intake of hypo‐palatable foods and hyper‐palatable SSBs. Additionally, it will explore the feasibility of MB in enhancing food preferences, energy intake, and dietary quality in a natural environment. The study consists of four phases. Phase 1 will employ a three‐arm pre‐post design to assess the effect of different doses of MB on the taste perception of individual food‐based solutions and single food items (measured using the generalized labeled magnitude scale, gLMS) in 54 healthy‐weight adults. Phases 2 and 3 will utilize a four‐arm, placebo‐controlled, pre‐post trial to determine the effective dose of MB that could change the taste perception (using gLMS), overall liking (using the labeled affective magnitude scale) and intake of hypo‐palatable mixed foods and hyper‐palatable SSBs in 40 healthy‐weight and 40 overweight/obese adults, respectively. Phase 4 will be a 12‐week, two‐arm, placebo‐controlled feasibility trial assessing the effect of MB on food preferences (food liking questionnaire), energy intake (3‐day food record and 24‐h dietary recall), dietary quality (Australian Recommended Food Score) and other feasibility indicators in 30 overweight/obese adults. Outcomes of phase 4 will be assessed at baseline, Week 1, Week 6, and Week 12. The effects of MB will be evaluated using mixed‐effects models, and a post hoc power analysis will be conducted.

AbbreviationsABSAustralian Bureau of StatisticsARFSAustralian Recommended Food ScoreBIABioelectrical Impedance AnalysisBMIBody Mass IndexEFSAEuropean Food Safety AuthorityFDAFood and Drug AdministrationFFMFat‐free MassFLQFood Liking QuestionnairegLMSGeneralized Labeled Magnitude ScaleHPLCHigh Performance Liquid ChromatographyIPAQInternational Physical Activity QuestionnaireLAMSLabeled Affective Magnitude ScaleMBMiracle BerryNCDsNon‐communicable DiseasesPROP6‐n‐propylthiouracilPTCPhenylthiocarbamideSSBsSugar Sweetened BeveragesTAS2R38Taste Receptor type 2 member 38WCWaist CircumferenceWHtRWaist‐to‐Height Ratio

## Introduction

1

Overweight and obesity are significant global public health issues (Global Burdon of Disease Collaborators 2017), and are major contributors to the rise of non‐communicable diseases (NCDs) such as Type 2 diabetes and other cardiovascular diseases (Goossens 2017; Tutor et al. 2023). The global economic burden of overweight and obesity is projected to exceed US$3 trillion annually by 2030 (World Health Organization (WHO) 2024).

Diet is a major modifiable determinant of overweight and obesity (Di Ciaula and Portincasa 2019) and NCDs (Al‐Jawaldeh and Abbass 2022); in particular, excessive intake of sugar‐rich foods and poor intake of core foods such as fruit and vegetables. Eating habits are shaped by a combination of biological (i.e., genetic) and environmental determinants, with taste preference being one of the primary motivating factors (Boesveldt et al. 2018). Humans have an innate liking for sweet‐tasting foods and a general aversion to sour and bitter tastes (Beauchamp 2016). This is often reflected in national food and nutrient consumption data, with large proportions of dietary energy intake coming from foods considered to be of little nutritional value (e.g., sugar‐sweetened beverages, SSBs). The data also suggest that the majority of the population consumes inadequate amounts of fruit and vegetables (Australian Bureau of Statistics 2022).

Adopting strategies that influence eating behaviors, perceptions, and food preferences is essential to effectively change dietary habits and improve dietary intake (i.e., reducing sugar consumption and increasing fruit and vegetable intake) (Mattei and Alfonso 2020; Pinho et al. 2018). While nutrition education has been widely used to address this issue, it often requires individualized counseling and has proven largely inefficient and unsustainable (Katenga‐Kaunda et al. 2022; Vasiloglou et al. 2019).

Non‐nutritive (low‐calorie) artificial sweeteners may be useful as a means of reducing sugar (and its associated energy) intake while maintaining flavor profiles (Sievenpiper et al. 2025). Many non‐nutritive sweeteners (NNS) are available (e.g., saccharin, aspartame, cyclamate, and acesulfame‐K) as low‐calorie alternatives to sugar (Mora and Dando 2021). Although NNS are approved as food additives and possess strong sweetness‐inducing potential (Samreen and Dhaneshwar 2023), their use may be accompanied by undesirable effects such as unpleasant aftertaste and intolerance symptoms (e.g., headache, nausea, vomiting, diarrhea, mood changes) (Ali et al. 2021; Bernardo et al. 2016). While NNS are considered safe within acceptable daily intake limits, uncertainties remain regarding their long‐term health consequences (Lohner et al. 2017). Meta‐analysis indicates that although few randomized controlled trials (RCTs) demonstrated modest short‐term benefits of NNS for weight reduction, findings from long‐term cohort studies suggest possible associations with adverse outcomes, including increased body mass index (BMI), Type 2 diabetes, and cardiovascular disease (Rios‐Leyvraz et al. 2022). Consequently, the WHO (2023) recommends limiting NNS use for weight management in favor of dietary strategies that naturally enhance sweetness. Regulatory bodies such as the U.S. Food and Drug Administration (FDA 2025) and the European Food Safety Authority (EFSA 2025), continue to affirm the safety of NNS within established limits, while acknowledging uncertainties regarding their long‐term effects. Additionally, artificial sweeteners primarily enhance sweetness and preserve palatability (Sievenpiper et al. 2025), but they are ineffective in reducing aversive taste qualities, such as sourness and bitterness. This limitation underscores the need for natural alternatives that not only enhance sweet taste perception but also mitigate these aversive attributes. Miraculin, in particular, exhibits this dual functionality and requires further investigation.

Miraculin is an active glycosylated protein extracted from the pulp of miracle berry (MB), also known as the miracle fruit (
*Synsepalum dulcificum*
 Daniell), a member of the Sapotaceae family (Misaka 2013). It comprises two glycosides attached to a single polypeptide chain with 191 amino acid residues (Kabore et al. 2022). Due to this active protein, MB has the unique ability to temporarily alter taste perception, making sour foods taste sweet (Diyapaththugama et al. 2024). This effect occurs from miraculin binding to taste receptors on the tongue and modifying how they respond to sour stimuli (Sanematsu et al. 2016). As a result, foods that are typically acidic (i.e., sour) can taste sweet after ingesting MB (Misaka 2013). Our previous review demonstrated that MB consistently decreases sourness and enhances sweetness in sour‐tasting solutions and food items. However, findings regarding its effects on bitter, salty, and sweet tastes remain inconsistent (Diyapaththugama et al. 2024). These discrepancies may stem from variations in experimental conditions, particularly considering that miraculin requires a pH range of 4.8–6.5 for activation (Akinmoladun et al. 2020; Doddawad et al. 2022).

The taste modification property of MB has generated considerable interest due to its potential to influence overall liking of hypo‐palatable fruits and vegetables, hyper‐palatable SSBs, and mixed meals. By reducing the aversive qualities of sour and bitter tastes, MB may increase the preference for such fruits and vegetables. Indeed, evidence indicates that MB enhances the overall liking of individual sour‐tasting foods (Choi and Garza 2021; Choi and Park 2023); however, its effect on the preference and intake of other hypo‐palatable foods with a bitter taste profile is yet to be investigated. Beyond sour and bitter foods, MB has been shown to enhance the sweetness of already sweetened binary and trinary mixtures (Capitanio et al. 2011), which may result in a sensation of oversweetness. Consumer research suggests that when sweetness surpasses optimal levels and reaches the rejection threshold, preference and intake decline, potentially contributing to lower sugar consumption (Peng et al. 2023). Despite this, no study has examined the role of MB on changes to the overall liking of hyperpalatable SSBs. Furthermore, since most foods are consumed as mixed meals, it is notable that only one randomized cross‐over trial has investigated the effect of MB on the overall liking of mixed meals (Choi and Park 2023). In this study, a 400 mg dose of MB was selected based on its previously demonstrated effectiveness in individual sour‐tasting foods (Choi and Garza 2020, 2021). The same dose significantly increased liking for breakfast and dinner meals, which were specific to Korean‐American cultural diets, but showed no significant effect for lunch. The authors suggested that the effective dose of MB for modifying taste perception and overall liking may vary depending on the type of food. To the best of our knowledge, no dose‐comparison study has been conducted on taste perception, overall liking and intake for mixed meals.

MB, as a potential NNS, also shows promise as a natural sugar substitute, with implications for reducing energy intake (Rodrigues et al. 2016). In a randomized, placebo‐controlled crossover trial among prediabetic and diabetic individuals, MB consumption lowered total energy intake by approximately 441 kJ compared with placebo (Choi and Park 2023). However, these findings were derived under controlled experimental conditions in which participants were provided with standardized meals, thereby limiting generalisability to real‐life settings. In addition, as MB has been reported to reduce the aversive perception of sour and bitter tastes (Andrade et al. 2019; Rodrigues et al. 2016), it may help facilitate healthier dietary patterns by improving the palatability of nutrient‐dense but under‐consumed sour and bitter fruits and vegetables. Collectively, these potential roles, attenuating energy intake and improving fruit and vegetable consumption, suggest that MB has potential to make a meaningful contribution to overall diet quality. However, to date, no study has examined these effects in real‐life settings.

Overall, as this project focuses on the taste‐modifying properties of MB, it is important to consider factors that may affect taste perception. Individuals with overweight or obesity often exhibit altered taste perception compared with those of healthy weight (Hajimaghsoodi et al. 2025; Peinado et al. 2023). These differences may influence the role of MB in modifying taste perception and food liking. To address this, the project is structured into four phases: the first two involve healthy‐weight adults to establish baseline effects of different MB doses on taste perception and liking, while the latter phases focus on adults with overweight or obesity, a population often encouraged to reduce added sugar intake and increase fruit and vegetable consumption (Koliaki et al. 2018). Furthermore, because both fruits and vegetables (Arias et al. 2022) and MB (Mosquera et al. 2025) possess antioxidant properties, assessing feasibility in adults with overweight or obesity may also provide additional health benefits, given their elevated risk of oxidative stress (Jakubiak et al. 2021).

## Aims and Objectives

2

This project aimed to investigate the taste modification properties of MB in adults living in Australia, addressing the following general objectives:
Assess the effect of different doses of MB on sour, bitter, tart, and sweet taste perception of individual food‐based solutions and food items in healthy‐weight adults living in Australia (Phase 1).Compare the effect of different doses of MB on sourness and bitterness taste perceptions, the overall liking and intake of hypo‐palatable mixed food, and the sweetness taste perception and overall liking of hyper‐palatable SSBs in healthy‐weight (Phase 2) and overweight/obese (Phase 3) adults living in Australia.Investigate the feasibility of using MB as a potential natural low‐calorie sweetener to modify food preferences, energy intake, and overall dietary quality in overweight/obese adults living in Australia (Phase 4).

## Methods and Materials

3

### Project Phases and Study Design

3.1

Each phase of the project will use different quasi‐experimental designs. Table 1 presents a summary of the study design, population, setting, variables, sample size, and study period for each phase.

**TABLE 1 fsn371640-tbl-0001:** Study designs, study populations, study settings, study variables, sample size and estimated study periods for each phase of the project.

	Project phases			
	Phase 1	Phase 2	Phase 3	Phase 4
Study design	Three‐arm pre‐post parallel design	Four‐arm placebo‐controlled single‐blind pre‐post parallel design	Four‐arm placebo‐controlled single‐blind pre‐post parallel design	Two‐arm placebo‐controlled, single‐blind (participants), parallel feasibility trial
Study population	Healthy‐weight adults living in Australia	Healthy‐weight adults living in Australia	Overweight or Obese adults living in Australia	Overweight or Obese adults living in Australia
Study setting	Laboratory‐based	Laboratory‐based	Laboratory‐based	In a natural environment (at home)
Independent variable	Different MB doses (175, 350, and 700 mg)	Different MB doses (175, 350, and 700 mg) and placebo	Different MB doses (175, 350, and 700 mg) and placebo	MB or Placebo consumption in a natural environment
Dependent variable	Sour, bitter, tart, and sweet taste perception ratings of food‐based solutions and individual food items	Ratings for sourness and bitterness taste perceptions, overall liking and intake of hypo‐palatable mixed vegetarian salad Ratings for sweetness taste perceptions and overall liking of SSBs	As mentioned in Phase 2	Primary outcomes Food preferences (Overall meal liking and preferences across time) Energy intake Dietary quality Other outcomes of interest Feasibility of the treatment protocol and study procedures Appetite Anthropometry/Body composition
Sample size	54	40	40	30
Proposed study period	1 July–30 September, 2024	1 November 2024–30 September 2025	1 December–30 June, 2025	1 May–30 December, 2025

*Note:* Sociodemographic characteristics (sex*, age, income, employment status, and education status), phenotypic taste perception, genotypic taste sensitivity, mouth pH, anthropometry, and body composition will be collected as covariates. In Phases 3 and 4, comorbidities (e.g., diabetes, hypertension) and medication use (self‐reported) will also be assessed. In Phase 4, physical activity will be measured as a covariate for secondary outcomes. *Sex is classified based on biological characteristics.

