*Note:* For non‐acidic solutions and food items (bitter and tart), we planned to use the solutions mixed with citric acid, as an acidic pH was essential for the taste modification action of miraculin (Doddawad et al. 2022). Food samples were kept in a refrigerator, then removed and placed on separate plastic trays 10 min before each test.

First, sociodemographic characteristics and anthropometric measurements will be collected. Saliva samples will then be obtained for TAS2R38 genotyping, and oral pH and phenotypic taste sensitivity will be assessed. As illustrated in Figure 1, participants (*N* = 54) will subsequently be allocated into three groups (*n* = 18 per group). Prior to commencing the pre‐test session, participants will be instructed to drink a sip of water and wait at least 30 s (Choi and Garza 2020). In their respective groups, participants will receive 10 mL of each solution and pieces of single food items to rate their perceived taste perception on a generalized labeled magnitude scale (gLMS). Participants will rinse their mouths with water between each solution or food item until the previous taste stimulus is gone (Igarashi et al. 2013; Lipatova and Campolattaro 2016).

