**FIGURE 1 fsn371640-fig-0001:**
[figure not shown]
Phase 1 study design.

After the pre‐test, participants will drink water to neutralize their mouths. Group A will receive 175 mg (half a tablet), Group B will receive 350 mg (one tablet), and Group C will receive 700 mg (two tablets) doses in MB tablets. Subjects will be instructed to dissolve the tablet with saliva on their tongue for 5 min and make contact with the tablet against as much surface area of the oral cavity as possible without chewing or swallowing it (Hudson et al. 2018). Immediately after dissolving, participants will receive the same solutions and food items used for the pre‐test to capture changes in perceived taste perception on gLMS.

#### Phase 2

3.7.3

A hypo‐palatable vegetarian salad containing half‐serve vegetables (raw broccoli and rocket leaves) and half‐serve fruits (Granny Smith apple), which are the minimum possible servings per Australian dietary guidelines (Brownie et al. 2015), will be prepared 30 min before the data collection time at Griffith University, Gold Coast campus kitchen lab or the Participants' home, based on the participants' preferences. Food items for the vegetarian salad and the Coca‐Cola (representing hyper‐palatable SSB) will be purchased from the local market. The food will be stored in a refrigerator (4°C), removed, and placed on separate plastic trays 10 min before each test. The SSB will be kept at room temperature, and 30 mL will be poured into 50 mL paper cups, which are clean and uniform in color (Mielby et al. 2018).

Figure 2 shows that participants (*n* = 40) will be allocated to four treatment arms (*n* = 10 in each group). The data collection procedure will follow these steps:

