
**FIGURE 2 fsn371640-fig-0002:**
[figure not shown]
Phases 2 and three study design.

#### Phase 3

3.7.4

The study design and data collection procedures followed in this phase are identical to those used in Phase 2 (Figure 2). They vary among study participants (Phase 2 is on healthy‐weight adults, and Phase 3 is on overweight or obese adults). A separate investigation is required because taste sensitivity alters with overweight and obesity (Harnischfeger and Dando 2021; Rohde et al. 2020; Vignini et al. 2019). Therefore, the dose of MB required to induce a change in taste perception and food liking may be different for overweight and obese adults than for healthy‐weight adults.

#### Phase 4

3.7.5

This will be a two‐arm, placebo‐controlled, single‐blind, parallel feasibility trial conducted over a 12‐week follow‐up period, in which participants will be blinded to group allocation. Blinding of participants will be maintained via the use of MB and Placebo tablets of similar size and closely matched colourings. Most importantly, participants will only receive their allocated treatment tablets and will not be privy to viewing the alternative treatment tablet. To minimize the risk of unblinding within households, only one participant per household will be enrolled. As this is a feasibility study, the success of blinding will also be evaluated by asking participants at the end of the trial whether they believed they had received MB or placebo.

The participants will have four visits to the Gold Coast campus, or they will be visited at their home by the principal investigator, based on their preference. That is, a first visit (at baseline), a second visit (at the end of the baseline week), a third visit (at the end of the 6th week), and a fourth visit (at the end of the 12th week). The main outcomes of interest are food preferences, energy intake, and dietary quality. Additionally, it will explore its effect on the overall liking of mixed meals (breakfast, lunch, dinner, and snacks) and on appetite. As it is a feasibility study, the other main outcomes of interest will be exploring the feasibility indicators (recruitment, blinding, allocation, retention, compliance, and adverse effects). Furthermore, as a secondary outcome, the study will investigate the effect of MB on anthropometry and body composition. Table 5 indicates the details of the study variables to be measured, including their frequency and the study visits at which they will be assessed.

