##### First Visit (Baseline Measurements)

3.7.5.1

At the first visit, baseline characteristics such as sociodemographic characteristics, phenotypic taste sensitivity, and physical activity will be measured. Food preferences will be measured using a validated Food Liking Questionnaire (FLQ), and dietary quality will be measured using the validated Australian Recommended Food Score (ARFS). Energy intake will be assessed using 3‐day food records supplemented with 24 h dietary recalls. To minimize errors in portion size estimation, participants will be instructed in the use of standardized and household measures. During the 24 h recall, participants will provide a detailed account of all foods and beverages consumed the preceding day, including brand names, ingredients, condiments, cooking methods, and portion sizes. Following the initial recall, the data collector (principal investigator) will probe for any omitted items, clarify portion sizes, and review the record jointly with the participant to ensure accuracy, with modifications made as required.

At the same visit, participants will be provided with a 3‐day food record sheet and instructed to record their intake over three non‐consecutive days (two weekdays and one weekend) during the following week. To improve accuracy, they will be encouraged to record portion sizes using package information or standardized measures and, when these are not feasible, to rely on household measures. Participants will also be advised to complete the record as soon as possible after each eating occasion to minimize underreporting and improve portion size estimations. The completed records will be reviewed by the researcher at the next visit for completeness and accuracy.

Furthermore, anthropometry and body composition will be measured as secondary outcomes of interest. During this initial visit, participants will be asked to provide their preferred way of contact (phone, email, or social media) and postal address (suburb, street, and postal code) for follow‐up purposes.

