##### Second Visit (End of Baseline Week)

3.7.5.2

In this visit, the 3‐day food record sheet provided in the first visit will be collected from study participants. Then, participants (*n* = 30) will be allocated into two arms. Then, participants will be given the required number of tablets (MB or placebo) in their respective groups for 6 weeks. Moreover, they will be provided with a 3‐day food record sheet and requested to complete it in the last week of this follow‐up period, before the third. Instructions will be provided to encourage participants to use a minimum amount of lime or lime juice while they administer tablets (to activate miraculin) with their meals in their daily lives. However, unlike the lab phases, no other strict standardization procedures will be imposed, as the aim is to evaluate the feasibility and acceptability of MB use in everyday dietary contexts.

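### Every phase is declared quasi-experimental and no random assignment is described, yet Phases 2 to 4 are analysed as placebo-controlled comparisons

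*Protocol article*

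**What the plan says.** **Design.** Section 3.1 opens with "Each phase of the project will use different quasi‐experimental designs". In Table 1, Phases 2 and 3 are each a "Four‐arm placebo‐controlled single‐blind pre‐post parallel design" and Phase 4 is a "Two‐arm placebo‐controlled, single‐blind (participants), parallel feasibility trial". None of the four design labels says randomised.

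**Assignment.** In section 3.7.2 (Phase 1) participants "will subsequently be allocated into three groups". In section 3.7.3 (Phase 2) they "will be allocated to four treatment arms". Section 3.7.4 says of Phase 3: "The study design and data collection procedures followed in this phase are identical to those used in Phase 2". At the second visit of Phase 4 (section 3.7.5.2) they "will be allocated into two arms". No sequence, concealment or stratification is described. The article uses the word randomized only for other groups' studies (Introduction and section 3.4.3).

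**Recruitment.** Section 3.5 specifies a convenience sample drawn from several routes.

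**Use of the arms.** The Abstract says Phases 2 and 3 are to determine the effective dose. Table 6 plans mixed models, Dunn-Šidák pairwise comparisons between doses and a 0.05 significance threshold, and an intention-to-treat analysis for Phase 4.

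**The concern.** Quasi-experimental is a positive description of a design without random assignment, so this is more than a detail left to a fuller document. The analysis, however, treats a difference between arms as the effect of the tablet or the dose. That reading needs arms that are comparable apart from chance, and the text describes nothing that would make them so. Intention to treat preserves comparability created at assignment; it cannot create it.

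The setting makes selection possible. Whoever assigns participants in Phase 1 already has their demographics, body measurements, mouth pH and phenylthiocarbamide (PTC) taster status. In Phase 4 the whole baseline assessment is complete. Phase 4 blinds participants only, and Phases 2 and 3 are single-blind.

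The effective-dose conclusion and the Phase 4 contrast with placebo are at stake. Phase 4 also counts allocation among its feasibility indicators. Without randomisation it cannot show whether random allocation would work in the larger studies that section 4 foresees. The limitations in section 4 concern self-reported diet and do not mention assignment.

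**Working it through.** **1. What is known at assignment, phase by phase**

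| Phase | Arms | Stated method | Known beforehand |
|---|---|---|---|
| 1 (3.7.2) | 3 doses, 18 each | none | Demographics, anthropometry, pH, PTC status; the pre-test ratings come afterwards |
| 2 and 3 (3.7.3, 3.7.4) | 4 arms, 10 each | none | Timing not given |
| 4 (3.7.5.2) | 2 arms, 15 each | none | Full baseline assessment and the baseline-week food record |

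**2. What pre-post measurement removes.** Write a participant's pre-tablet rating as *m + a* and the post-tablet rating as *m + a + t + c*. Here *a* is the person's stable level, *t* the tablet effect, and *c* the change that would have occurred anyway (repetition, satiety, expectation, or a different response to the test).

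- Change = *t + c*, so *a* cancels.
- Difference in change between two arms = difference in *t* + difference in mean *c*.

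A stable difference in level, such as tasters finding the salad more bitter at both tests, therefore drops out, provided the contrast is one of change (dose by time). A systematic difference in *c* stays in. Covariates could reduce that part where they are measured, but section 3.4.2 keeps age, sex and PTC sensitivity only if they help model stability and fit. Control of confounding is therefore not assured.

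**3. Size.** The documents give no figure for a systematic difference in *c*, so the bias cannot be computed. The following is an assumption only, to show sensitivity. Suppose there is no true effect and the arms differ systematically by *b* standard deviations of change. For a two-sided 5% two-sample t-test on change, the noncentrality is *b* × √(n/2) with 2n − 2 degrees of freedom:

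| *b* (SD of change) | 10 per arm | 15 per arm |
|---|---|---|
| 0 | 5.0% | 5.0% |
| 0.2 | 7.1% | 8.3% |
| 0.5 | 18.5% | 26.2% |
| 0.8 | 39.5% | 56.2% |

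For example, with n = 10 and *b* = 0.5 the noncentrality is 0.5 × √5 = 1.12. These are false-positive rates for one comparison, before any multiplicity correction.

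**4. Effect of randomising on sample size.** The plan's figures reproduce, and none depends on how participants are assigned:

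- Phase 1: 3 × 18 = 54, from a within-group paired calculation.
- Phases 2 and 3: 10 per predictor × 4 = 40 each.
- Phase 4: 10 / (1 − 0.32) = 14.7, rounded up to 15 per arm; 2 × 15 = 30.

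Randomising to the same equal arms leaves 54, 40, 40 and 30 as they are.

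**The case against.** **The method may be stated elsewhere.** Sections 3.7.2 and 3.7.3 refer to Figures 1 and 2, and section 3.7.5.6 refers to Table S5 for how the feasibility indicators are measured. None of these could be seen, and a condensed article often leaves sequence generation to the full protocol. This has force: a reader might infer that participants were certainly not randomised, and the text does not prove that. But if one of those places describes random allocation, section 3.1 contradicts it and still needs correcting.

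**Pre-post measurement and covariates give protection.** They do. A reader might infer that taster imbalance feeds directly into the arm contrast, or that no analysis could help. Neither follows: stable differences cancel from change, and PTC status is measured and is a candidate covariate. Differential change and unmeasured factors remain.

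**Timing and assessment.** A reader might infer that arms are always assigned with the pre-tablet ratings in hand. Phase 1 forms the groups before those ratings, and Phases 2 and 3 do not give the timing. Nor does the investigator's probing at the first Phase 4 visit show bias by arm, because it precedes allocation. Unblinded assessment after allocation is a question of detection bias, separate from this one.

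**A non-randomised study may have a placebo arm and p-values, and Phase 4 is a feasibility trial.** Both are true. The difficulty is the strength of the conclusion, not the presence of a placebo.

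**Conclusion.** The point stands in this form: the plan declares a non-random design, describes no random assignment, and still draws dose and placebo conclusions that need comparable arms. The same weakness affects the between-dose comparisons in Phase 1, which has no placebo arm.

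The size of the bias is unknown, and the illustrative rates rest wholly on assumed differences in change. The text does not say who assigns participants; an unblinded investigator doing so is the natural reading, not a stated fact. Randomising would remove systematic selection. Chance imbalance with 10 to 15 per arm would remain, so adjustment for the baseline value is still worthwhile.

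A reader might also infer that the defect can be cured in every phase by amendment. Table 1 dates Phase 1 to July to September 2024, and the article cites 2025 sources, so Phase 1 was probably complete when the article was written. Later phases may also have been allocated. For those, only the label, the analysis and the wording can change.

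**What to change.** **Participants not yet allocated.** Replace quasi-experimental with randomised in section 3.1, and allocated with randomly allocated in sections 3.7.2 to 3.7.5. Use a computer-generated permuted-block list for each phase, prepared in advance and held in sequentially numbered opaque envelopes. Keep the block sizes from the person enrolling. Open each envelope only after the pre-tablet ratings (Phases 1 to 3) or after the baseline week (Phase 4). In Phase 1 this moves group formation to after the pre-test.

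**If allocation was in fact random.** Correct the label in section 3.1 and state the method.

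**Phases already allocated non-randomly.** Label them non-randomised, restrict causal and effective-dose wording, and adjust for the pre-tablet or baseline value and for PTC status, whether or not these improve model fit. Add the assignment method to the limitations in section 4.

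**Cost.** For future allocations: a short amendment and about an hour to prepare the lists, with no extra participants, visits or staff. For completed phases: revised text and a pre-specified adjusted model.
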